## Methods: data collection, management, and analysis

### Plans for assessment and collection of trial data {25a}

Outcome data will be collected from all participants, including participants who withdraw from the intervention wherever possible. Furthermore, participants will be thanked with an honorarium of £20 once they complete their second SCID-5 assessment to improve data collection and completeness. In addition, for participants who withdraw or who are difficult to contact, multiple efforts will be made by the research team to reach these participants and invite them to complete measures at all data collection timepoints. Attempts will be made through different modalities (i.e. email, telephone, SMS) in case participants change contact information or are more accessible through one modality. The research team will continue to contact hard-to-reach participants throughout the trial until they complete outcome data or they withdraw consent from being sent outcome measure invitations. Shortened versions of questionnaires will also be made available to participants to complete, which will contain the most important measures (i.e. PCL-5 and PHQ-9) to reduce the potential burden on participants who struggle to complete follow-up measures. An additional monetary incentive (£10 e-voucher) for filling out a shortened questionnaire (PCL-5 and PHQ-9) will be issued for particularly hard-to-reach participants who do not respond to any contact method and who have not completed either the self-report measures or SCID-5 assessment at any post-randomisation timepoint. Most of the outcome data will be collected using Qualtrics [57], a widely used data collection online software programme. Participant outcome data on Qualtrics will be pseudonymised by participant ID. Access to the outcome data will be restricted to the main study team (JL, JW, CC, AE, and AM) using a secure login (two-factor authentication). To minimise data entry errors and ensure completeness, data validation procedures including force response settings and single-choice restrictions will be implemented within the Qualtrics survey platform where applicable. The only data that will not be collected over Qualtrics is the SCID-5 assessment measures collected at baseline, 8 weeks post-random allocation, and 6 months post-intervention completion as well as the semi-structured interviews. This data will be in the format of interview recordings, online SCID-5 assessment sheets, and online topic guides that will be safely stored in restricted access folders on Nexus 365 OneDrive for Business, only accessible by the main study team. Data completeness and anomalies will be checked on a weekly basis by the trial lead (JL), and any issues will be flagged and brought to weekly supervision with the PI (JW) to be resolved on a case-by-case basis.

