### Plans to promote participant retention and complete follow-up {25b}

To support retention and prevent dropouts, participants and prospective participants will receive a £10 e-voucher as an honorarium for each SCID-5 assessment they complete (4 assessments for the waitlist condition, 3 assessments for the intervention condition, and 1 assessment for prospective participants found to be ineligible). Participants will be able to spend their e-voucher on a variety of brands.

Participants are allowed to withdraw at any stage of the trial and ask for their data to be deleted. Their future treatment in NHS and private services will not be affected by withdrawing from the study. Withdrawal after randomisation will be recorded along with reasons (if provided). Participants who withdraw from the intervention or waitlist condition will continue to be sent follow-up questionnaires unless they withdraw their consent for this.

Participants who do not respond to initial invitations to take part in SCID-5 assessments will be contacted using a variety of available approaches (email, phone call, SMS) unless they have withdrawn their consent from the trial. Participants who are reluctant to complete the longer questionnaires or the SCID-5 assessments at 4 weeks post-random allocation, 8 weeks post-random allocation, or 6 months post-intervention completion will be sent the PCL-5 and PHQ-9 as a minimum dataset.

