## Statistical methods

### Statistical methods to compare groups for primary and secondary outcomes, including harms {27a and 27b}

Consistent with the BMJ and Consolidated Standards of Reporting Trials guidelines, all analyses will be intent-to-treat (ITT) from randomisation, whereby participants will be analysed under the same conditions as they were randomly assigned, irrespective of the treatment they actually received, subsequent willingness, adherence, or completion of follow-up outcome measures. Primary and secondary main trial analyses will be conducted once all willing participants in both conditions have completed their 8-week post-random allocation SCID-5 assessment and questionnaires. Follow-up analyses will be conducted at the conclusion of the trial period (i.e. after all willing participants in both conditions have completed their 6-month post-intervention follow-up SCID-5 assessment and questionnaires).

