##### Secondary outcomes

All secondary outcome analyses will be treated as exploratory analyses.

Between-group analyses of the continuous secondary outcome measures will include mixed effects regression models and multiple regression models following the same specifications as the primary outcome measure with additional fixed effects for time, a time by condition interaction, and a random effect for participant for the mixed-effect regression models. Mixed effects regression models allow for the inclusion of all available data from randomised participants (ITT), can account for missing data, and can account for repeated measures [67]. Between-group effect sizes (Cohen’s *d*) will be calculated by dividing the adjusted group difference by the baseline standard deviation.

For secondary outcome measures collected at 4 and 8 weeks post-random allocation (i.e. PCL-5, PHQ-9, GAD-7, PTCI-s, and RIQ-s), statistical models of treatment effects will include categorical fixed factors of time (4 weeks, 8 weeks post-random allocation), condition (SHAPE, waitlist), and the time × condition interaction. The interaction permits the estimation of differences between treatments at each timepoint. Participant will be treated as a random effect to account for between-participant variation.

For secondary outcome measures collected at 8 weeks post-random allocation only (i.e. ISI, ITQ, WEMWBS, CD-RISC, and social support scales), we will fit multiple regression models including condition (SHAPE, waitlist).

The stratification variables absence/presence of PTSD assessed with the SCID-5 at baseline, depression symptom severity (<15 or 15) assessed at baseline with the PHQ-9, and time since reported trauma (>/<18 months) assessed at baseline with the PCL-5 will be included as fixed covariates, along with the baseline score of the measure being analysed. Significance level will be set to *p* < 0.05 for comparison between the SHAPE and waitlist conditions.

To assess for potential correlates of PTSD and MDD symptom change, we will conduct correlational analyses to assess the strength of the relationship between change in posttraumatic cognitions and maladaptive responses to intrusions from baseline to week 4, and from baseline to week 8 and change in PTSD and MDD symptom severity over the same time periods, controlling for baseline scores on these measures. This analysis will be conducted with the whole sample at week 8 to include post-intervention and post-wait participants.

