### Methods in analysis to handle protocol non-adherence and any statistical methods to handle missing data {27c}

For the primary outcome, if missing data is <5%, this will be handled with complete case analysis whereby participants with missing data at the primary outcome timepoint (8 weeks post-randomisation) will be excluded from the analysis. If missing data is >5%, multiple imputation will be employed.

Due to the secondary analyses being exploratory in nature, no sensitivity analyses will be conducted to test assumptions for missing data. However, the statistical analysis methods used for the secondary measures are able to handle missing data under a data missing at random assumption.

More information on handling protocol non-adherence and missing data is included in the statistical analysis plan [68].

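### The missing-at-random statement for secondary outcomes is too broad for the week-8-only regressions, which ignore PCL-5 and PHQ-9 scores returned on the short form

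*Protocol article*

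**What the plan says.** All places are in the protocol article.

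- **Model** (Main trial analyses, Secondary outcomes): "For secondary outcome measures collected at 8 weeks post-random allocation only (i.e. ISI, ITQ, WEMWBS, CD-RISC, and social support scales"), the plan is "we will fit multiple regression models including condition (SHAPE, waitlist"). The three minimisation factors "will be included as fixed covariates, along with the baseline score of the measure being analysed". No follow-up PCL-5 or PHQ-9 score enters these models. The same section credits the use of all available data to the mixed models, not to these regressions.
- **Short form** ({25a}): "Shortened versions of questionnaires will also be made available to participants to complete, which will contain the most important measures (i.e. PCL-5 and PHQ-9"). Under {25b}, participants reluctant to do the longer questionnaires or the diagnostic interview "will be sent the PCL-5 and PHQ-9 as a minimum dataset".
- **Missing data** ({27c}): multiple imputation is named for the primary outcome. For the secondary outcomes, "no sensitivity analyses will be conducted to test assumptions for missing data", the reason given being that they are exploratory. The text then says that "the statistical analysis methods used for the secondary measures are able to handle missing data under a data missing at random assumption". It refers to the statistical analysis plan for more information.

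**The concern.** Missing at random means that missingness may depend on anything observed. A likelihood-based mixed model uses the observed repeated values of the measure it analyses. A regression of one week-8 score has no such second source. Unless missing scores are imputed, a participant without that score drops out of the fit. The estimate is then unbiased only under a narrower condition: given arm, the minimisation factors and the measure's own baseline, missingness is unrelated to the outcome.

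A participant who returns only the short form at week 8 has no ISI, ITQ, WEMWBS, CD-RISC or social support score, but does have observed week-8 PTSD and depression severity. If severity at that time influences who completes the long form, the data can still be missing at random given everything collected, yet the planned regression can be biased because it leaves that severity out. At stake are the effect estimates for insomnia, complex PTSD, wellbeing and resilience, all of which appear in the trial's stated hypotheses.

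**Working it through.** **The plan's own figures.** The protocol gives no figure for missing secondary outcomes. Its only related numbers are the sample size and the 15% attrition. With 50% versus 84% not recovered, two-sided 5% and 90% power, the mean proportion is 0.67 and

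n = [1.960 × √(2 × 0.67 × 0.33) + 1.282 × √(0.25 + 0.1344)]² / 0.34² = (1.303 + 0.795)² / 0.1156 ≈ 38.1, so 39 per arm.

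Then 78 / 0.85 = 91.8, so 92. Both figures reproduce and neither is affected by this point.

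**Where the bias comes from.** Let e_Y be the outcome residual given arm and model covariates, and e_P the week-8 PCL-5 residual. Then

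bias = mean(e_Y among completers, SHAPE) − mean(e_Y among completers, waitlist).

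If missingness acts through e_P, and the residual correlation is ρ with equal variances, this becomes

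bias = ρ × [mean(e_P among completers, SHAPE) − mean(e_P among completers, waitlist)].

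An equal shift in both arms cancels. Bias needs a mechanism that differs by arm.

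**Size under assumed inputs.** The documents supply none of the following, so all are assumptions:

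- 92 participants, within-arm outcome SD 1, lower score better, true adjusted effect −0.50 SD;
- correlation of the outcome with its own baseline 0.5, so residual SD = √0.75 = 0.866;
- ρ of 0.4, 0.6 or 0.8;
- log-odds of a missing long form changing by 1 per residual SD of week-8 PCL-5, where dependence is present;
- week-8 PCL-5 observed for everyone.

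Bias of the regression without imputation, in SD (1,500 simulated trials per cell):

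| Dependence on week-8 PCL-5 | Missing | ρ = 0.4 | ρ = 0.6 | ρ = 0.8 |
|---|---|---|---|---|
| SHAPE arm only | 6% | −0.024 | −0.033 | −0.046 |
| SHAPE arm only | 12% | −0.044 | −0.061 | −0.084 |
| SHAPE arm only | 17% | −0.055 | −0.084 | −0.112 |
| SHAPE arm only | 22% | −0.074 | −0.106 | −0.139 |
| Opposite in the two arms | 7% | −0.046 | −0.070 | −0.094 |
| Opposite in the two arms | 24% | −0.139 | −0.211 | −0.284 |

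With no dependence, or the same dependence in both arms, the bias was never more than 0.005 SD in size.

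The results follow the formula, being proportional to ρ. At 17% missing, 0.055/0.4, 0.084/0.6 and 0.112/0.8 are all 0.14. The negative sign (benefit overstated) reflects the assumed direction, with more severe SHAPE participants skipping the long form. Reversing the direction would reverse the sign.

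A second simulation took a true effect of 0.60 SD, ρ = 0.7 and 11–16% missing. It gave 0.579 with the same mechanism in both arms, and 0.650 and 0.691 with mechanisms that differed. The differences from 0.600 are −0.021, +0.050 and +0.091.

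**With the short-form scores used.** In the first simulation, regression imputation from arm, own baseline, and baseline and week-8 PCL-5 left a bias of at most 0.003 SD in every scenario. In the second, imputation using week-8 PCL-5 returned 0.597, 0.601 and 0.599. This recovery is built in, because the variable that drives missingness is in the imputation model. It shows that the bias is removable if severity is the driver, not that severity is the driver.

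**Against sampling error.** With 39 per arm the standard error is about 0.866 × √(2/39) = 0.196 SD. The one-arm range of 0.02 to 0.14 SD is therefore about 0.1 to 0.7 of a standard error (0.02/0.196 and 0.14/0.196). The opposite-direction extreme of 0.28 is about 1.4.

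**The case against.** - **The SAP may deal with it.** No passage prescribes complete-case analysis for these outcomes. It is inferred from a one-timepoint regression with no imputation named. The secondary models are also said to share the primary outcome's specification, which could be read as carrying imputation over, and {27c} points to the SAP. Silence in an article would be no finding. What remains is printed: {27c} separates primary from secondary outcomes, names imputation only for the primary, excludes missing-data sensitivity analyses for the rest, and asserts validity under missing at random.
- **The statement is imprecise rather than false.** Covariate-adjusted regression is valid under one form of missing at random. That stands, and it is why the point is about the breadth of the sentence.
- **The short form helps.** A reader might infer that the minimum-dataset rule causes the missingness. It does not: it is offered to people already reluctant to do the long form and recovers data that might otherwise be lost. Nor are the PCL-5 and PHQ-9 known for all of them, since forms are sent and not necessarily returned.
- **Intention to treat.** A reader might also infer a breach of the promise to analyse irrespective of "completion of follow-up outcome measures". The documents do not support that. Participants are still analysed by allocated arm, and any single-timepoint model with missing outcomes falls short of the literal wording to the same degree.
- **Nothing shows that missingness differs by arm.** Correct. A difference is plausible, because the Waitlist condition section ties access to SHAPE to finishing the end-of-wait measures and second assessment, an incentive that the SHAPE arm lacks. It remains unproven.
- **The 15% attrition is not a short-form rate.** Also correct. The number of short-form-only participants is unknown.

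**Conclusion.** The point holds in a limited form. For ISI, ITQ, WEMWBS, CD-RISC and social support, the missing-at-random statement in {27c} is too broad. The planned regressions need missingness to depend only on arm and their own covariates, and they leave out follow-up severity scores that the retention plan sets out to collect.

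The bias cannot be sized from the documents. Under the stated assumptions it is about zero if the mechanism is the same in both arms, roughly 0.02 to 0.14 SD if only one arm is affected, and up to about 0.28 SD if the arms go in opposite directions. That these estimates will be biased, or biased in SHAPE's favour, does not follow.

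The outcomes are declared exploratory, and the primary analysis and sample size are untouched. This is a cheap improvement, not a threat to the trial's main conclusion.

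**What to change.** 1. Extend multiple imputation to the week-8-only outcomes. Impute separately by arm, with the analysis covariates plus baseline, week-4 and week-8 PCL-5 and PHQ-9 as auxiliary variables. With 46 randomised per arm, the imputation model should stay close to that list.
2. Report the regressions without imputation alongside, and give by arm the number with the long form, the short form only, and neither.
3. Limit the {27c} statement to the mixed models. For the single-timepoint regressions, say that validity without imputation requires missingness to depend only on arm and the covariates in the model.
4. If the reference to the primary outcome's specification was meant to include imputation, say so.

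The cost is a little more analysis work, since imputation is already planned for the primary outcome. No new data are needed. There is no gain for participants with no follow-up data, and outcomes missing for reasons unrelated to the observed scores are not corrected.

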##### Secondary outcomes

We predict that the SHAPE intervention will be superior to the waitlist condition by achieving significantly greater change in clinical symptoms (i.e. PTSD, MDD, GAD, C-PTSD, and insomnia) at 8 weeks post-treatment allocation. We also predict that the SHAPE intervention will be superior to the waitlist condition by achieving significantly greater change in wellbeing, resilience, and quality of life measures at 8 weeks post-treatment allocation. For the correlates of change analysis, we hypothesise that changes in cognitive processes (posttraumatic cognitions, maladaptive responses to intrusive memories) from baseline to mid-intervention (week 4) will predict the extent of PTSD and MDD symptom reduction (week 8), controlling for baseline scores. We hypothesise that changes in cognitive processes (posttraumatic cognitions, maladaptive responses to intrusive memories) from baseline to week 8 will correlate with PTSD and MDD symptom reduction from baseline to post-intervention (week 8), controlling for baseline scores.

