### Sample size {19}

The sample size for the randomised controlled trial was calculated based on 90% power, at a significance level (*α*) of 0.05, to detect a difference in proportions of the number of participants continuing to have PTSD and MDD at 8 weeks post-random allocation. An anticipated recovery rate of 50% of participants in the intervention condition (i.e. 50% not recovered) and 16% of participants in the waitlist condition (i.e. 84% not recovered) corresponds to a relative risk of 0.59, requiring 39 participants per condition (78 in total). Allowing for up to 15% attrition increases the required sample size to *N* = 92 (46 participants per condition).

The effect size (50% recovery) for the intervention condition was informed by the NHS Talking Therapies target of 50% recovery for all individuals completing treatment [36]. This is a conservative estimate as findings from the pilot study of SHAPE comparing participants scores on the PCL-5 and PHQ-9 found recovery rates of 77.1% and 64.3% for MDD and PTSD respectively ([name], [name], Wilkins A, Storch C, Browne H, & [name]. Cognitive therapy coaching for PTSD and depression symptoms in healthcare workers repeatedly exposed to trauma: a pilot evaluation of SHAPE, under review). We chose a 50% recovery rate in line with the NHS Talking Therapies target and to allow for greater power for the secondary analyses. The effect size (16% recovery) for the waitlist condition was based on previous studies documenting natural recovery rates for PTSD and MDD over a 2–3-month period of between 12 and 20% for both disorders [37–40]. The 15% attrition estimate was based on dropout rates of similar trials and studies reporting rates of between 10 and 20% [37, 41–47].

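### The first correlates-of-change hypothesis (week-4 cognitive change predicting week-8 symptom reduction) has no matching analysis in the article, which pairs changes over the same periods only

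*Protocol article*

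**What the plan says.** Under Hypotheses, Secondary outcomes, the protocol article makes two predictions about cognitive processes.

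- **First hypothesis (lagged).** Change in these processes "from baseline to mid-intervention (week 4) will predict the extent of PTSD and MDD symptom reduction (week 8), controlling for baseline scores".
- **Second hypothesis (concurrent).** Change in these processes "from baseline to week 8 will correlate with PTSD and MDD symptom reduction from baseline to post-intervention (week 8), controlling for baseline scores".

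Under Statistical methods, Main trial analyses, Secondary outcomes, the article sets out correlational analyses of change in posttraumatic cognitions and "maladaptive responses to intrusions from baseline to week 4, and from baseline to week 8", on one side, and "change in PTSD and MDD symptom severity over the same time periods, controlling for baseline scores on these measures", on the other. It adds: "This analysis will be conducted with the whole sample at week 8 to include post-intervention and post-wait participants". The only covariates named for this analysis are baseline scores. The same section labels all secondary outcome analyses exploratory.

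The data for either analysis are planned. The section describes its repeated-measures models as being "For secondary outcome measures collected at 4 and 8 weeks post-random allocation (i.e. PCL-5, PHQ-9, GAD-7, PTCI-s, and RIQ-s"), and the Measures section places all four relevant instruments (PCL-5, PHQ-9, PTCI-s, RIQ-s) at baseline, week 4 and week 8.

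**The concern.** The two hypotheses use different windows and different verbs: one says that earlier change predicts a later outcome, the other that two changes correlate. The lag in the first therefore looks deliberate. The analysis text then ties symptom change to the same window as cognitive change, and the lagged pairing disappears.

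An analyst who follows the article as written would compute a 0–4 with 0–4 correlation that nobody hypothesised and would leave the first hypothesis untested. The 0–4 result could then be taken as the answer to the first hypothesis, although it estimates something else. At stake is whether the trial answers one of its own stated exploratory questions. The randomised comparison is not involved.

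**Working it through.** **Step 1: set the pairings side by side.**

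| Cognitive change | Symptom change | Stated as a hypothesis? | Stated as an analysis? |
|---|---|---|---|
| weeks 0–4 | to week 8 | yes, the first | no |
| weeks 0–8 | weeks 0–8 | yes, the second | yes |
| weeks 0–4 | weeks 0–4 | no | yes |

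**Step 2: test the reading that would close the gap.** The sentence on the whole sample at week 8 could be read as making week 8 the outcome for both predictors. It goes on to explain that post-intervention and post-wait participants are included, so it describes who is analysed and when. Read as setting the outcome, it would contradict the statement that symptom change covers the same periods.

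**Step 3: ask whether the mismatch matters numerically.** The article gives no figure for this analysis, so there is nothing to reproduce. The following is an illustration. Every parameter in it is assumed; none comes from the documents.

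Let c be the cognitive score and s the symptom score at weeks 0, 4 and 8:

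- c4 = 0.6·c0 + 0.6·e, and c8 = 0.6·c4 + 0.6·g
- s4 = φ·s0 + 0.6·f, and s8 = φ·s4 + b·(c4 − c0) + 0.6·h

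The terms e, f, g, h have unit variance; e and f correlate at ρ, as do g and h, and all other pairs are independent. φ is symptom carry-over and b is a true lagged effect of cognitive change.

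After adjustment for c0 and s0, and division by 0.6, what remains is: cognition 0–4, e; symptoms 0–4, f; cognition 0–8, 0.6e + g; symptoms 0–8, φf + be + h. Write V = φ² + b² + 2φbρ + 1. Then:

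- same window 0–4: r = ρ
- lagged (cognition 0–4, symptoms 0–8): r = (φρ + b)/√V
- same window 0–8: r = [0.6(φρ + b) + ρ]/√(1.36·V)

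*Scenario A: concurrent link only, no carry-over* (ρ = 0.75² = 0.5625, φ = 0, b = 0, V = 1).
- 0–4 with 0–4: 0.56
- lagged: 0/1 = 0.00
- 0–8 with 0–8: 0.5625/√1.36 = 0.48

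*Scenario B: concurrent link only, carry-over 0.6* (ρ = 0.5625, φ = 0.6, b = 0, V = 1.36).
- 0–4 with 0–4: 0.56
- lagged: 0.3375/√1.36 = 0.29
- 0–8 with 0–8: (0.2025 + 0.5625)/1.36 = 0.56
- lagged, also adjusting for week-4 symptoms: 0.00, because only h remains and it is unrelated to e

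*Scenario C: lagged effect only* (ρ = 0, φ = 0.6, b = 0.5, V = 0.36 + 0.25 + 1 = 1.61).
- 0–4 with 0–4: 0.00
- lagged: 0.5/√1.61 = 0.39
- 0–8 with 0–8: 0.3/√(1.36 × 1.61) = 0.20
- lagged, also adjusting for week-4 symptoms: 0.5/√1.25 = 0.45

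A simulation of 200,000 participants under the same model gave the same values to two decimals.

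**Step 4: read the result.** With baseline adjustment alone, as the first hypothesis specifies, the planned 0–4 correlation can be sizeable when the lagged association is zero (A), and zero when the lagged association is real (C). It cannot stand in for the first hypothesis.

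**The case against.** The best case for the plan has four parts.

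- **The statistical analysis plan may hold the lagged model.** The article says that a detailed plan is public and supplied as a supplementary file. This stands as a limit: one can say only that no matching analysis is stated in this article. It does not remove the point, because the article does more than leave the model open. It specifies pairings that differ from its own hypothesis.
- **The sentence is condensed.** It lists two cognitive windows and the same periods for symptoms without saying respectively, so cross-pairing is not expressly ruled out. It remains the less natural reading, and a reader should not have to guess.
- **The analysis is exploratory and is described as correlational.** This is true and limits the weight of the point. It does not explain why a specific, time-ordered prediction is stated and then not tested.
- **A lagged correlation would not settle direction either.** This is right. In scenario B the baseline-adjusted lagged correlation is 0.29 with no lagged effect at all, and it vanishes only when week-4 symptoms are added.

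The last part also bears on a stronger reading that a reader might infer: that the plan is at fault for not separating cognition driving symptoms from the reverse, or that a concurrent result will be presented as evidence of how SHAPE works. The documents support neither. The first hypothesis controls for baseline scores only and makes no claim net of week-4 symptoms. The objectives speak of exploring potential correlates, and no mediation analysis is announced. Conditioning on week-4 symptoms asks about residual change between weeks 4 and 8, which is a different and debatable question.

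**Conclusion.** The point holds as an inconsistency between two stated parts of the article. One of the two correlates-of-change hypotheses has no matching analysis, and one planned correlation has no hypothesis. It would be wrong to infer that the whole correlates analysis misses its target, because the 0–8 with 0–8 pairing fits the second hypothesis exactly.

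The conclusion rests on the plain reading of the text and needs no numerical assumption. The illustrative correlations (0.56 against 0.00, and 0.00 against 0.39) show only that the two quantities can diverge in either direction; they are not estimates for this trial. The importance is moderate. The text should be corrected so that the trial can answer its own question, but the primary outcome, the sample size and the randomised comparisons are untouched.

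**What to change.** In Main trial analyses, Secondary outcomes, give each hypothesis its own analysis.

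- **First hypothesis.** Regress week-8 PCL-5, and separately week-8 PHQ-9, on baseline-to-week-4 change in PTCI-s and RIQ-s, adjusting for the baseline symptom score and the baseline process scores. Change from baseline to week 8 may serve as the outcome instead; with the baseline symptom score in the model, the coefficient on cognitive change is the same. State whether the two process measures enter together or in separate models.
- **Condition.** Because both arms are pooled, include condition as a covariate. If SHAPE shifts cognitions and symptoms alike, the difference between arms alone would otherwise contribute to the association.
- **Second hypothesis.** Keep the 0–8 with 0–8 correlation.
- **The 0–4 with 0–4 correlation.** Drop it, or label it as descriptive and tied to no hypothesis.
- **Optional.** Add week-4 symptom score as a sensitivity analysis to probe time order, and state that it answers a different question.

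If the lagged analysis is not wanted, reword the first hypothesis as concurrent. In either case, check the statistical analysis plan for the same pairing.

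The cost is a change of wording and a few additional models. All the measures are already scheduled at baseline, week 4 and week 8 in both arms.

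### The correlates-of-change analysis pools both arms and controls only for baseline scores, so a SHAPE effect on both process and symptom measures would inflate the correlation

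*Protocol article*

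**What the plan says.** The protocol article (Statistical methods, Main trial analyses, Secondary outcomes) describes the method: "we will conduct correlational analyses to assess the strength of the relationship between change in posttraumatic cognitions and maladaptive responses to intrusions". The changes run from baseline to week 4 and from baseline to week 8, and are related to "change in PTSD and MDD symptom severity over the same time periods, controlling for baseline scores on these measures". The sample is both arms together: "This analysis will be conducted with the whole sample at week 8 to include post-intervention and post-wait participants".

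The matching hypothesis (Hypotheses, Secondary outcomes) names the same single control. Change in cognitive processes to week 8 "will correlate with PTSD and MDD symptom reduction from baseline to post-intervention (week 8), controlling for baseline scores". The companion hypothesis, that cognitive change by week 4 predicts later symptom reduction, also names only baseline scores.

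Neither place mentions condition, a within-arm estimate or an interaction with arm for this analysis. The treatment-effect models in the same section do name it: "condition (SHAPE, waitlist), and the time × condition interaction". The section opens with "All secondary outcome analyses will be treated as exploratory analyses".

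**The concern.** Adjusting for baseline scores does not remove the effect of arm here. Randomisation balances baseline in expectation; where the arms are expected to differ is in change. If SHAPE lowers both a process score and a symptom score, the pooled scatter of changes consists of two displaced clusters, and a positive correlation appears even when the two changes are unrelated inside each cluster.

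The trial expects to be near that situation. It predicts that SHAPE will be "superior to the waitlist condition by achieving significantly greater change in clinical symptoms". It gives no between-arm prediction for the process scales, but it models them for treatment effects alongside the symptom scales: "i.e. PCL-5, PHQ-9, GAD-7, PTCI-s, and RIQ-s), statistical models of treatment effects will include categorical fixed factors of time". Several tools in Table 2 (for rumination, unhelpful thoughts, guilt and self-blame) address content that the RIQ-s and PTCI-s measure.

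At stake is the reading of the process hypotheses. A correlation carried partly by arm membership repeats the treatment comparison made elsewhere in the section, and says less than it seems to about whether people whose cognitions change more also improve more. The abstract says that findings will inform adaptations of the intervention, so the distinction has some practical weight.

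**Working it through.** **The plan's own figure.** The article states no figure for the correlates analysis, so only the sample size can be reproduced. Inputs from Sample size {19}: recovery 50% against 16%, 90% power, α 0.05 (taken as two-sided). The pooled mean is 0.33.

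- n per arm = [1.960 × √(2 × 0.33 × 0.67) + 1.282 × √(0.50 × 0.50 + 0.16 × 0.84)]² / 0.34² = (1.303 + 0.795)² / 0.1156 ≈ 38.1, so 39 per arm and 78 in total, as stated.
- 78 / 0.85 = 91.8, so 92, as stated.

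I therefore take 78 analysed (39 per arm) as the planned case and 92 (46 per arm) as the case of no loss.

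**Assumption on effect size.** The article gives no effect size for PCL-5, PHQ-9, PTCI-s or RIQ-s. Let d_x and d_y be the arm differences in process change and symptom change, in within-arm SDs of change. As a rough anchor only, 50% against 16% recovery corresponds to d ≈ 0.99 on a probit scale (0 − (−0.994)) or 0.91 on a logit scale (ln 5.25 × √3/π). That concerns diagnosis, not the process scales. The protocol's own Cohen's d divides by the baseline SD, so values on that scale do not carry over directly.

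**Formula.** With 1:1 arms and within-arm correlation ρ, the arm split adds d_x·d_y/4 to the covariance and d²/4 to each variance:

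r = (ρ + d_x·d_y/4) / √[(1 + d_x²/4)(1 + d_y²/4)].

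With ρ = 0 and d_x = d_y = d, this is (d²/4)/(1 + d²/4):

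- d = 0.5: 0.0625/1.0625 = 0.06
- d = 0.8: 0.16/1.16 = 0.14
- d = 1.0: 0.25/1.25 = 0.20
- d = 1.2: 0.36/1.36 = 0.26

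**Chance of p < 0.05 by Fisher z, n = 78.** The standard error is 1/√75 = 0.1155. For d = 0.8, 1.0 and 1.2, atanh(r)/SE is 1.20, 1.76 and 2.35, giving 23%, 42% and 65%.

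**Simulation.** This took the partial correlation of change scores adjusted for both baselines, as the article describes, with ρ = 0 and 4,000 runs per setting. Shares of runs with p < 0.05:

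| d on both | no condition term, 39 per arm | no condition term, 46 per arm | condition added (39; 46 per arm) |
|---|---|---|---|
| 0 | 5% | 5% | 5%; 5% |
| 0.5 | 7% | 9% | 4%; 5% |
| 0.8 | 22% | 25% | 5%; 5% |
| 1.0 | 41% | 49% | 6%; 5% |
| 1.2 | 66% | 73% | 5%; 5% |

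Adjusting for baseline leaves the artefact in place; adding condition removes it.

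**Boundary cases.**

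- Effect on one measure only (d = 1 and 0): r = 0, and p < 0.05 in about 4% of runs. No artefact.
- Unequal effects, such as a smaller shift in cognitions by week 4 (0.5 and 1.0): r = 0.125/√(1.0625 × 1.25) = 0.11.
- A real within-arm link, ρ = 0.30 with d = 1 on both: pooled r = (0.30 + 0.25)/1.25 = 0.44. In simulation, 0.44 without condition and 0.30 with it.

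**The case against.** The best defence is that the article promises only correlates, labels all secondary analyses exploratory and nowhere claims mediation. A whole-sample association that includes the difference between arms is a legitimate description, and adding condition changes the question to a within-arm one. This stands as far as it goes. But the article attaches directional process hypotheses to these correlations, and for those the within-arm association is the informative quantity. An exploratory label excuses multiplicity; it does not correct a known bias.

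Second, the article sets p < 0.05 for comparisons between conditions and states no threshold for the correlations. The rejection rates above therefore describe a test that a reader would probably apply, not one that the plan fixes. That stands.

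Third, large equal effects on both measures are an assumption. At d = 0.5 the rate is close to nominal, and by week 4 the arm difference may be smaller. That also stands and limits the size of the point.

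Fourth, the separate analysis plan is not shown and may include condition. It may. But the article does not leave the matter open: it states the pooled sample and the controls, and condition is not among them. If the analysis plan differs, the article needs aligning.

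A reader might go further and infer that the analysis would confirm the process hypotheses whenever SHAPE works on both scales. The figures do not support that: at d = 0.8 about three trials in four would still miss p < 0.05. Nor does it follow that an observed pooled correlation is spurious; a real within-arm link may lie beneath an inflated estimate.

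**Conclusion.** The point holds as a conditional bias in a stated secondary analysis. Followed as written, the pooled correlation is pushed upward if SHAPE moves both the process and the symptom measure, and is unaffected if it moves only one. Under the assumed equal d, the bias is minor at 0.5 and material from about 0.8. The chance of apparent confirmation is raised, not certain. The primary outcome, the sample size and the treatment-effect estimates are untouched. It should be corrected, but it does not threaten the trial's main conclusion.

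**What to change.** Add condition as a covariate, with the baseline scores, in every correlates model, for the week 4 and the week 8 changes. Amend the correlates paragraph under Statistical methods and the process hypotheses under Hypotheses so that both name it. The whole sample is kept.

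Arm-specific correlations and a condition × process-change interaction are optional and should be descriptive only. With 39 per arm, the standard error on the Fisher z scale is 1/√36 = 0.17, so a 95% interval spans roughly ±0.33.

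The cost is one degree of freedom and no new data. Significant results will also be fewer: with ρ = 0.30 and d = 1 at 39 per arm, p < 0.05 fell from 98% of runs to 75%. The difference is signal that the pooled version takes from the arm contrast.
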